### Consent procedure

Eligible patients are informed about the study by a member of the clinical team or research staff and written information sheet is provided. After a consideration of at least 24 hours, the patient is contacted to enquire whether the patient is willing to participate in the study. At the screening visit, a written information consent approved by the local ethics committee is obtained from all participants before any trial-related procedures are performed.

### Randomisation

Randomisation will be via a bespoke 24-hour web-based randomisation system hosted at the King’s Clinical Trials Unit (KCTU). Patients will be randomised at the level of the individual, using the method of minimisation incorporating a random element. The minimisation factors will be HbA1C (< 7.999% (63.89 mmol/mol or below) or ≥8% (69.90 mmol/mol or above), perifoveal or parafoveal location of baseline zone of increased retinal thickness of ≥320 μm (parafoveal zone 2 to 5 or perifoveal zone 6 to 9) and study site. If both parafoveal and perifoveal zone thickening co-exist, it will be categorised as parafoveal.

Patients may only be randomised into the study by an authorised member of staff at the study site as detailed on the delegation log. Participants may only be randomised into the study once.

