### Statistical analysis

The primary outcome will be analysed using a two-sided test from a linear mixed effect model for repeated measures across visits, which will enable a comparison between participants receiving light-masks (active) and control masks, with covariates for each follow-up visit of baseline, randomisation stratifier and arm, and with a random participant effect at each visit with unstructured covariance matrix. The primary time-point will be 24 months. The 20% allowance for dropout (trial withdrawal) is based on 18% early non-compliance observed in the pilot study and we would expect a reasonable proportion of non-compliers to provide primary time-point and intermediate visit outcome information for this analysis.

We expect the DMEC would want to monitor study power and we would regularly provide information such as non-compliance, withdrawal, and variability of the primary outcome with increasing certainty as increasing proportions of the participants pass each of the 4-monthly measurement points.

The detailed statistical analysis plan will include an additional sensitivity analysis involving all randomised participants (intention to treat strategy) examining the influence on the primary outcome analysis of opposing optimistic and pessimistic scenarios for the intervention effect in those withdrawing in each arm. We will adopt the complier average causal effects (CACE) analysis (under a missing at random assumption) as recommended and outlined by Dunn *et al*.
[15].

Linear mixed effect models for repeated measures (as specified above for the primary outcome), logistic regression, and stratified Cox regression, will also be undertaken to analyse secondary and mechanistic outcomes of continuous, binary and time to occurrence type respectively. Differences will be considered significant at *P* < 0.05. Differences between the groups will be estimated with 95% confidence intervals. Repeated measure analyses (linear mixed effects models) will be used to document trends over time.

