## Trial status

The trial has started recruiting.

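### The mmol/mol figures for the two HbA1c minimisation categories are 6.01 apart although the percent figures meet at 8%: the upper figure, 69.90, should be about 63.9

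*Protocol article*

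**What the plan says.** The Randomisation section of the protocol article allocates patients "using the method of minimisation incorporating a random element" through a web-based system, with three factors: HbA1c, location of the thickened zone, and study site. The HbA1c factor has two levels, each given in both units: "HbA1C (< 7.999% (63.89 mmol/mol or below) or ≥8% (69.90 mmol/mol or above". The section does not say which unit governs or which one is entered into the system.

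The Statistical analysis section describes the primary mixed model "with covariates for each follow-up visit of baseline, randomisation stratifier and arm". It does not list which minimisation factors the stratifier term covers. Table 1 shows HbA1c measured at baseline, 12 and 24 months. The Trial status section reports: "The trial has started recruiting".

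**The concern.** The two units are meant to express one split. The percent figures differ by 0.001 of a percentage point, but the mmol/mol figures beside them differ by about 6. Both pairs cannot describe the same boundary, and nothing elsewhere in the article says which is intended.

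This is a threshold in a working allocation rule, applied by staff at 15 or more sites. If the mmol/mol figure is used in practice, patients with the same HbA1c could be coded differently according to the unit in which it was reported. Minimisation would then balance a partly mislabelled factor. The same label could pass into the primary model, if the stratifier term includes HbA1c.

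**Working it through.** **1. Check from the document alone.**

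- Lower category: 7.999%, paired with 63.89 mmol/mol.
- Upper category: 8%, paired with 69.90 mmol/mol.
- Step in percent: 8 − 7.999 = 0.001.
- Step in mmol/mol: 69.90 − 63.89 = 6.01.

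The slope implied between the two boundaries is 6.01 / 0.001 = 6,010 mmol/mol per percentage point, which is impossible for a change of unit. At least one mmol/mol figure is wrong.

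**2. Which figure is wrong.** This needs the conversion between the units, which the article does not give. I assume the standard linear form, mmol/mol = 10.929 × (% − 2.15).

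- 7.999%: 10.929 × 5.849 = 63.92. The article prints 63.89, so this figure reproduces to within 0.04.
- 8%: 10.929 × 5.850 = 63.93. The article prints 69.90, which is about 6 too high.
- In reverse, 69.90 / 10.929 + 2.15 = 8.55%, and 63.89 / 10.929 + 2.15 = 8.00% (7.996%).

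The other common form, (% − 2.152) / 0.09148, gives 63.92 for 7.999%, 63.93 for 8% and 8.55% for 69.90 mmol/mol. The result does not depend on the variant. Stepping on from the article's own 63.89 gives 63.90, so 69.90 looks like a one-digit slip.

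**3. Who is affected.** The range from about 63.9 to 69.9 mmol/mol is about 8.0% to 8.55%.

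| Rule as printed | Category of a patient at 65 mmol/mol |
|---|---|
| Percent | Upper (8% or more) |
| mmol/mol | None (above 63.89, below 69.90) |

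**4. How many could lie in the range.** The article gives no HbA1c distribution. I assume a normal one, with mean 56 to 72 and SD 14 to 20 mmol/mol. The share is Φ((69.9 − mean)/SD) − Φ((63.9 − mean)/SD).

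| Mean | SD | Share in range | Of 300 |
|---|---|---|---|
| 56 | 20 | 0.7565 − 0.6536 = 10.3% | 31 |
| 60 | 20 | 0.6897 − 0.5773 = 11.2% | 34 |
| 64 | 17 | 0.6357 − 0.4977 = 13.8% | 41 |
| 68 | 14 | 0.5540 − 0.3848 = 16.9% | 51 |

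Over the whole assumed grid the share runs from 10.3% to 17.0%, or 31 to 51 patients. This counts patients whose HbA1c lies in the range. It does not count patients misclassified.

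**5. Sample size.** Two-sided 5% level, 90% power, difference 15 μm and SD 35.7 μm give 120 per arm, 240 in all, and 240 / 0.8 = 300 after 20% dropout. The article's figures reproduce, and the HbA1c cut-off plays no part in them.

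**The case against.** The strongest reply is that no operational harm is shown. The article does not say which unit the system takes, whether it derives the category itself, or whether 69.90 appears in it at all. The slip may exist only in the article. The percent rule stands on the same line and classifies every patient in the gap. All of this stands, so the consequence must be stated as conditional.

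Three stronger readings are tempting, and the document supports none of them:

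- **That patients in the gap are put in the lower category.** The printed lower category ends at 63.89 mmol/mol, so a patient at 65 is not in it. By the printed mmol/mol rule this patient has no category. Coding the patient as low would be a guess about what a site does.
- **That the treatment comparison is biased.** The category is set before allocation and cannot depend on the arm. Miscoding would weaken balance on one prognostic factor and blur one covariate. If the unit varied by laboratory, it would probably vary mainly by site, and site is itself a minimisation factor.
- **That HbA1c is certainly a covariate in the primary model.** The Statistical analysis section refers to the stratifier in the singular and does not name HbA1c. Its inclusion is a reasonable inference, no more. Even then, HbA1c is recorded at baseline, so the covariate can be recoded at analysis.

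What the reply does not remove is the contradiction itself. The sentence is complete, and no other part of the article corrects it.

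**Conclusion.** The upper mmol/mol cut-off is wrong as written. The inconsistency follows from the article alone; that 69.90 is the faulty figure rests on the standard unit conversion. Patients between about 63.9 and 69.9 mmol/mol (8.0% to 8.55%) are in the upper category in one unit and uncategorised in the other.

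Whether this touched any allocation depends on a fact not given, namely the unit and cut-off in the randomisation system. If it classifies by percent, allocation is unaffected. If it or the sites classify by mmol/mol, the cost is weaker balance on HbA1c and an inconsistently coded stratification covariate, if HbA1c is part of that term. The randomisation stays valid and the planned sample size stands. The 10% to 17% of patients in the range depends on the assumed distribution and is an upper bound on exposure; the number misclassified is unknown and may be zero. Severity is minor to moderate: a real error in a working rule, cheap to correct, with no demonstrated effect on the primary comparison.

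**What to change.** State the categories as below 8% and 8% or above, with mmol/mol values that meet: 63.89 or below, and 63.90 or above. Writing the lower category as below 8% also closes the trivial gap between 7.999% and 8%.

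Because recruitment has begun:

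1. Confirm which unit and cut-off the web randomisation system uses, and correct its specification if 69.90 appears there.
2. Check how patients already entered with 63.9 to 69.9 mmol/mol were coded, and record what is found.
3. If HbA1c enters the analysis models as a stratification factor, derive its category from the recorded baseline HbA1c with the corrected cut-off, and fix this before any unblinded analysis.

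The cost is one figure in the protocol, a check of the system specification and a short data listing. No allocation has to be undone and no sample-size change is needed.

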**Method/Design:**

This is a phase III randomised controlled single-masked multicentre clinical trial to test the clinical efficacy of light-masks at preventing dark-adaptation in the treatment of non-central DMO. Three hundred patients with non-centre-involving DMO in at least one eye will be randomised 1:1 to light-masks and control masks (with no light) to be used during sleep at night for a period of 24 months. The primary outcome is regression of non-central oedema by assessing change in the zone of maximal retinal thickness at baseline on optical coherence tomography (SD-OCT). Secondary outcomes will evaluate the prevention of development and progression of DMO by assessing changes in retinal thickness in different regions of the macula, macular volume, refracted visual acuity and level of retinopathy. Safety parameters will include sleep disturbance. Adverse events and measures of compliance will be assessed over 24 months. Participants recruited to the mechanistic sub-study will have additional retinal oximetry, multifocal electroretinography (ERG) and microperimetry to evaluate the role of hypoxia by assessing and comparing changes induced by supplemental oxygen and the light-masks at 12 months.

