### Patient recruitment

Patients may be identified from diabetic retinopathy screening programmes and medical retina clinics of the trial sites and its satellite clinics. In addition, patients may be referred by other medical retina consultants from other hospitals to the Principal Investigators (PIs). In order to prevent patients from being subjected to unnecessary trial procedures, it is recommended that potential participants have an SD-OCT done at their clinic visit or at a pre-screening clinic before trial screening procedures are done to ensure exclusion of eyes with centre-involving macular oedema defined as central subfield > 300 μm.

We will report on the numbers of eligible patients informed of the study, the numbers screened and the numbers who were recruited into the study.

Inclusion criteria are:Subjects of either sex aged 18 years or overDiagnosis of diabetes mellitus (type 1 or type 2). Any one of the following will be considered to be sufficient evidence that diabetes is present:Current regular use of insulin for the treatment of diabetesCurrent regular use of oral anti-hyperglycaemic agents for the treatment of diabetesDocumented diabetes by ADA and/or WHO criteriaBest corrected visual acuity in the study eye better than 55 ETDRS letters (Snellen VA 6/24)On clinical exam, retinal thickening due to early DMO not involving the central 1000 μm of the macula characterised by presence of microaneurysm, exudates or oedema and OCT evidence of increased retinal thickness in at least 1 non-central ETDRS zone of ≥320 μm.Previous macular laser, intravitreal steroids or anti-VEGF treatment is permitted provided the last laser treatment was done at least 4 months before date of recruitment or anti-VEGF treatment was done at least 2 months previouslyMedia clarity, pupillary dilation and subject cooperation sufficient for adequate fundus photographsAbility to return for study visitsAbility to give informed consent throughout the duration of the study

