### Outcomes

The primary efficacy measure is the difference between arms in the change from baseline in absolute retinal thickness at the zone of maximum thickness as determined by OCT at 24 months.

The secondary efficacy parameters at 12 and 24 months are:

Efficacy parameters:I.Difference between arms in the change from baseline in absolute thickness at the zone of maximum thickness as determined by OCT at 12 months.II.Other measures include: Difference between arms in the change in retinal thickness in the 9 ETDRS zones (parafoveal zones 2-5 and perifoveal zones 6-9) and macular volume.Difference between arm in morphological characteristics of macular thicknessDifference between arms in the mean change in visual acuity.Difference between arms in the proportion of centre-involving macular oedema within 24 months.Difference between arms in the time to occurrence of centre-involving macular oedema.Difference between arms in the proportion requiring macular laser or antiVEGF treatment.Difference between arms in the proportion of participants that show progression of retinopathy as measured by the ETDRS severity levels and microaneurysm turnover.Compliance rates in the light mask arm.

II. Assessment of Safety Parameters {XE “6.2 Procedures for Assessing Efficacy Parameters”}Difference between arms in the measures of sleep disturbance in terms of daytime sleepiness and insomnia.Difference between arms in ocular and systemic adverse events and serious adverse events.

III. Assessment of Mechanistic Parameters {XE “6.2 Procedures for Assessing Efficacy Parameters”}Change in P1 and N1 amplitudes and peak time in multifocal ERG after supplemental oxygenChange in retinal sensitivity in scotopic microperimetry after supplemental oxygen.To determine differences in change in P1 and N1 amplitudes and peak time in multifocal ERG after light-masks and dummy masks at 12 months.To determine differences in change in retinal sensitivity in scotopic microperimetry after light-masks and dummy masks at 12 months.To correlate the changes induced by light-masks and oxygen supplementation on retinal sensitivity using oximetry.

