### Sample size calculation

With 300 patients (150 in each arm), we anticipate 240 to be followed up (20% dropout). This is sufficient to provide 90% power to detect 15 μm in mean change of retinal thickness at the zone of maximal thickness between arms using a 2-sided test, adjusting for baseline, at the 5% level of significance, assuming a standard deviation of 35.7 μm. The chosen detectable effect size (retinal thickness of 15 μm) is both plausible, in terms of being consistent with a confidence interval estimate for this intervention in preceding research (Ruboxistaurin trial protocol: B7A-MC-MBCU), and also minimally detectable in terms of being distinguishable from test-retest variation [25]. Detectable effect sizes for secondary outcomes based on 240 followed up (for 90% power with 5% significance level) would be a between-arm difference in mean outcome of a size that is equivalent to 0.42 of a standard deviation.

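### In eyes with both rings thickened, the randomisation location factor can differ from the ring of the zone analysed; adding that ring as a baseline covariate is a small, optional gain in precision

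*Protocol article*

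**What the plan says.** The Randomisation section lists three minimisation factors: HbA1c category, study site and the "perifoveal or parafoveal location of baseline zone of increased retinal thickness of ≥320 μm (parafoveal zone 2 to 5 or perifoveal zone 6 to 9". For eyes with thickening in both rings it adds: "If both parafoveal and perifoveal zone thickening co-exist, it will be categorised as parafoveal". The factor thus records where thickening is present, not where it is greatest.

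The Outcomes section defines the primary measure as the between-arm difference in the "change from baseline in absolute retinal thickness at the zone of maximum thickness as determined by OCT at 24 months". The abstract fixes that zone at baseline ("assessing change in the zone of maximal retinal thickness at baseline on optical coherence tomography (SD-OCT"), as does the Objectives section. None of these places restricts it to one ring. The secondary outcome at 12 months uses the same zone.

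Eligibility requires "OCT evidence of increased retinal thickness in at least 1 non-central ETDRS zone of ≥320 μm", so an eye may have several thick zones, in one ring or both.

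The Statistical analysis section specifies a mixed model for repeated measures "with covariates for each follow-up visit of baseline, randomisation stratifier and arm". The stratifier is singular and not named. Location is the likely reading for at least one of the terms meant, but this is not spelled out.

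**The concern.** Two baseline descriptions of the same eye are built by different rules. One, presence of thickening with the parafoveal ring taking precedence, drives the balancing and, on the likely reading, the adjustment. The other, the thickest zone, decides which measurement is analysed. They disagree in one direction only: an eye whose thickest zone is perifoveal, but which also has a parafoveal zone at 320 μm or more, is coded parafoveal.

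The parafoveal category therefore mixes eyes analysed at a parafoveal zone with eyes analysed at a perifoveal zone. If 24-month change differs between rings, neither the minimisation nor the coded covariate separates the two groups, and that variation stays in the residual. Adjusting for baseline thickness does not identify the ring either. At stake is some precision in the primary comparison.

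**Working it through.** **1. The plan's own figure.** Inputs from Sample size calculation: difference 15 μm, SD 35.7 μm, two-sided 5%, 90% power, 20% dropout.

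- n per arm = 2 × (1.960 + 1.282)² × 35.7² / 15² = 119.04, rounded up to 120
- 240 followed up; 240 / 0.8 = 300 randomised, as stated
- 15 / 35.7 = 0.42 SD, as stated
- power at 120 per arm: 90.2% by the normal approximation, 90.0% by the t distribution

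Location does not enter this calculation.

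**2. When the two definitions disagree.**

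| Zones at 320 μm or more | Thickest zone | Coded as | Ring analysed |
|---|---|---|---|
| Parafoveal only | Parafoveal | Parafoveal | Parafoveal |
| Perifoveal only | Perifoveal | Perifoveal | Perifoveal |
| Both | Parafoveal | Parafoveal | Parafoveal |
| Both (e.g. 322 and 380 μm) | Perifoveal | Parafoveal | Perifoveal |

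Only the last row is discordant.

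**3. Removable variance.** The article does not give these quantities, so they are assumptions:

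- q, the share of eyes that are discordant: 10–30%
- d, the difference in 24-month change between rings: 10–20 μm, with 30 μm as an extreme
- 40% of eyes have a perifoveal maximum, so the share coded parafoveal is P = 0.6 + q
- 35.7 μm is the residual SD with the coded factor already in the model

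Discordant eyes all lie in the parafoveal-coded group, where they form a fraction q/P. The variance of the true ring that the coded factor leaves unexplained is P × (q/P) × (1 − q/P) = q(1 − q/P). The share of residual variance removed by adding the ring is q(1 − q/P) × d² / 35.7², where 35.7² = 1274.49. Power is by the t distribution, 120 per arm, with the reduced SD.

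| d (μm) | q | q(1 − q/P) | Share removed | SD (μm) | Power |
|---|---|---|---|---|---|
| 10 | 0.1 | 0.086 | 0.7% | 35.58 | 90.2% |
| 10 | 0.2 | 0.150 | 1.2% | 35.49 | 90.3% |
| 10 | 0.3 | 0.200 | 1.6% | 35.42 | 90.4% |
| 20 | 0.1 | 0.086 | 2.7% | 35.22 | 90.8% |
| 20 | 0.2 | 0.150 | 4.7% | 34.85 | 91.3% |
| 20 | 0.3 | 0.200 | 6.3% | 34.56 | 91.8% |
| 30 | 0.3 | 0.200 | 14.1% | 33.08 | 93.8% |

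Against 90.0%, the gain for ring effects of 10–20 μm is about 0.2–2 points.

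**4. Validity of adjusting for the factor as coded.** Simulation of 240 participants: balance forced on the coded factor, true effect −15 μm, q = 0.1–0.3, d = 0–20 μm, 40% perifoveal maximum, 4,000 runs per setting. The analysis was a single-time-point ANCOVA, a simplification of the planned repeated-measures model.

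- Mean estimate, adjusting for the coded factor: −14.9 to −15.1 μm
- Type I error: 0.044 to 0.055
- Power: 0.88–0.91 with the coded factor, 0.89–0.91 with the analysed ring
- Largest difference: 0.879 against 0.901, at q = 0.3 and d = 20 μm
- At d = 0, no gain from the analysed ring

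Here 35.7 μm is the SD after removing the ring effect, so the same precision appears as a loss of about 2 points rather than a gain.

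**5. Chance imbalance in the analysed ring.** At q = 0.3 and d = 20 μm it contributes an SD of 20 × √(0.200 × 2/120) = 1.15 μm to the treatment estimate. The standard error of that estimate is 35.7 × √(2/120) = 4.61 μm. In variance terms, 1.15² = 1.33, which is 6.3% of 4.61² = 21.2. This is the share already in the table of step 3, not an additional cost.

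**The case against.** The strongest reply is that nothing here is an error. The precedence rule is explicit, applied before randomisation and identical in both arms. Adjusting for a factor as it was used in minimisation is standard practice, and no sentence says the factor should represent the analysed ring. All of that stands, and step 4 supports it. A reader might infer that the primary model adjusts for a wrong location and is therefore biased. The document does not support that reading.

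A reader might also infer that planned power is lost. It is not: the calculation rests on 35.7 μm after baseline adjustment, and location plays no part. Nor is chance imbalance a second harm, as step 5 shows; the standard error already covers it.

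The article gives no reason for including location. A parafoveal-first rule would also fit an aim of balancing closeness to the centre, since centre-involving oedema is a secondary outcome. A ring effect on thickness change is therefore an assumption, and 30 μm would be twice the difference the trial is powered to detect.

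Finally, covariate detail is commonly left to the statistical analysis plan, which is not shown. This carries weight against calling anything missing. It does not dispose of the point, because the article does fix both the precedence rule and the covariate set. The same reply does defeat an extension to HbA1c: the article does not say how HbA1c is coded in the model, and no gain from a continuous term can be shown.

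**Conclusion.** The mismatch follows from the protocol's own definitions: in eyes with both rings thickened, the location factor need not describe the zone analysed. The consequence is limited to precision. The treatment estimate stays unbiased, type I error stays near 5%, and the sample size and its 90% power stand.

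The gain from adjusting for the analysed ring is about 0.2–2 points of power if 10–30% of eyes are discordant and rings differ by 10–20 μm in 24-month change. It reaches 93.8% power only at 30% discordance with a 30 μm ring effect, and it is nil if ring has no effect. These figures rest wholly on assumed discordance, ring effect and share of perifoveal maxima. This is a minor point: an inexpensive improvement, not the repair of a defect.

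**What to change.** Leave the minimisation, its precedence rule and its factors in the model unchanged. Pre-specify one further baseline covariate in the primary analysis and in the 12-month analysis of the same outcome: the ring (parafoveal, zones 2–5, or perifoveal, zones 6–9) of the zone thickest at baseline. Derive it from the pre-randomisation OCT and enter it by visit, like the other covariates. Because the recruitment section sets out to exclude central subfields above 300 μm and requires a non-central zone of at least 320 μm, the thickest zone should fall in one of the two rings. State this before unblinding, since adding it later would be post hoc.

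The cost is one line in the statistical analysis plan and about one degree of freedom per visit, or six coefficients over the OCT visits at months 4, 8, 12, 16, 20 and 24. No new data are needed, because the zone must be identified at baseline anyway to define the outcome.
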